#### Statistical analysis

For our first two research aims, statistical analyses will be done on an intention-to-treat basis, with differences between study arms in mean changes in SBP and FRS as the primary outcomes. Participant characteristics and rates of recruitment, retention, and intervention fidelity will be summarized by using descriptive statistics. To test the hypothesis that the intervention will lead to significantly more reduction in SBP and FRS relative to the control condition, mean changes in SBP and FRS between baseline and 3-month and 6-month follow-up will be analyzed by independent t-tests between the 2 arms. Analysis of covariance and general linear modeling approaches will then be used to adjust for relevant covariates, such as gender, age, type of community, and baseline SBP and FRS values. Missing values for SBP and FRS at follow-up visits will be imputed by carrying forward baseline observations. If a covariate value is missing, it will be assumed to be missing at random. For sensitivity analyses, mean changes in SBP and FRS of participants who complete follow-up data collection will be analyzed by using a complete case analysis method. A stratified analysis will also be conducted within site or by gender to explore the potential impact of such factors on outcomes. In addition, data collected at all study visits will be modeled by repeated measures analysis of variance and linear mixed effects models, incorporating correlated data from multiple visits, to examine the post-intervention maintenance of SBP and FRS improvements. Determination of the appropriate covariance matrix in the repeated measure analysis will be based on quality of fit to the data by using the method of Fitzmaurice et al. [73]. Statistical analyses will be performed in SAS 9.4 (2015 SAS Institute Inc.). A two-tailed *p*-value <0.05 will be regarded as statistically significant.

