#### Power analysis and sample size

Our proposed target of 250 enrolled participants (125 per arm) is based on an anticipated attrition rate of 20%. To test the efficacy of the intervention, our sample size calculation was based on mean differences in SBP in our pilot study [42], which demonstrated a 3-month mean change in SBP of 7.5 mmHg (SD = 16.5) between 2 arms randomized 1:1. Assuming that 206 participants (103 per arm) complete all follow-up assessments, we will have 90% statistical power to detect a similar effect size in our ongoing study.

Although we plan to compare CVD scores between the tow study arms, no FRS data specific to the Native Hawaiian population are available. Therefore, we used data from a previous community-based intervention to calculate the necessary sample size. In a 1-year study with a multiethnic sample recruited in medically underserved urban and rural communities (*n* = 195; 59% White, 37% Black, and 4% Hispanic), the biggest changes in FRS were observed at month four [59]. The reported average reduction in FRS varied according to differences in initial risk profiles – for example, 6.0% (SD = 9.9%) for participants at high risk (FRS ≥ 20) and 1.3% (SD = 4.5%) for participants at intermediate risk (20 > FRS ≥ 10). Among study participants, 63% had HTN, with baseline averages of SBP = 146 mmHg and DBP = 82 mmHg, almost identical to the baseline averages in our pilot study (SBP = 146 mmHg, DBP = 86 mmHg). Given a similar mean change in FRS for participants at intermediate risk, a sample of *n* = 206 will provide 80% statistical power to detect a change in FRS of 1.3% (SD = 4.5%) at 6-month follow-up.

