Another innovation of this study is our analysis of psychosocial and sociocultural constructs (e.g., cultural identity, perceived ethnic discrimination) that might mediate the intervention effect on BP control. Our pilot study found that the intervention reduced perceptions of racism, and preliminary findings of other ongoing studies indicate that Native Hawaiian ethnic identity is positively related to behavioral and emotional self-control. Thus, our design responds to a transdisciplinary call for studies of the mechanisms underlying behavioral interventions [80–82].

Our ongoing study also has limitations. First, implementing the intervention at several different sites makes it difficult to ensure the consistency in delivery required by standardization, and might therefore introduce confounders into our analyses. To minimize this possibility, we will conduct fidelity checks and offer booster training sessions as needed. Second, we rely on self-report measures for many variables of interest, potentially introducing biases involving recall and social desirability. Nevertheless, self-report is the primary method of assessing attitudes, beliefs, and other cognitive processes, and we will use measures validated in previous studies with Native Hawaiians to minimize self-reporting biases. Third, we anticipate that more women than men might participate, since dancing might be more attractive to women. Accordingly, we will make special efforts to recruit Native Hawaiian men to achieve balanced gender representation.

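### Site and gender are explored only by separate stratified analyses, which do not test whether the effect differs; adding interaction terms to the planned models would do so at no cost

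*Protocol article*

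**What the plan says.** The protocol article's Statistical analysis section has one sentence on whether site or gender matters: "A stratified analysis will also be conducted within site or by gender to explore the potential impact of such factors on outcomes".

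In the same section, mean changes in SBP and FRS "will be analyzed by independent t-tests between the 2 arms", and ANCOVA and general linear models then "adjust for relevant covariates, such as gender, age, type of community, and baseline SBP and FRS values". Gender and type of community enter there as adjustment variables. No product of arm with site or gender is mentioned.

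The only significance rule is general: "A two-tailed *p*-value <0.05 will be regarded as statistically significant". The stratified analyses are not exempted from it.

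On gender numbers the Discussion says "we anticipate that more women than men might participate", and adds that special efforts will be made to recruit men so as to reach balance. The expected split is not given.

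**The concern.** Whether site or gender changes the intervention effect is a question about a difference between effects. Separate analyses within strata give one effect estimate per stratum and no measure of how far those estimates differ beyond chance. If each stratum is then labelled significant or not, the label depends heavily on the stratum's size: with one common effect, a large stratum will tend to pass 0.05 and a small one will tend to fail.

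The design makes small strata certain for site, because five sites share the sample, and unequal strata possible for gender. The Discussion lists consistency of delivery across sites and low male participation among the study's limitations, so readers will look for these two contrasts. A pattern of benefit at some sites but not others, or in women but not men, could be taken as real when it reflects only stratum size.

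**Working it through.** **Inputs from the article**
- SBP: "3-month mean change in SBP of 7.5 mmHg (SD = 16.5) between 2 arms randomized 1:1" (Power analysis and sample size).
- Completers: 206, that is 103 per arm (same section).
- FRS: difference 1.3, SD 4.5 (same section).
- Two-sided 0.05 (Statistical analysis).
- Five sites (Recruitment), 1:1 allocation within site (Study design).

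**Assumptions**
- The true effect is identical in every stratum.
- Sites are of equal size.
- The share of women is between 50% and 80%.
- Strata are read as significant or not at 0.05.

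**Step 1. The plan's own SBP figure.** The article states: "Assuming that 206 participants (103 per arm) complete all follow-up assessments, we will have 90% statistical power to detect a similar effect size". The noncentral t-test with n = 103 per arm and standardised effect 7.5/16.5 = 0.455 gives 90.1%. The figure reproduces. For FRS only the difference and SD are used below; the stated "80% statistical power to detect a change in FRS of 1.3% (SD = 4.5%) at 6-month follow-up" is a separate matter, since a two-arm comparison with these inputs has about 54% power.

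**Step 2. Power within a stratum.** Noncentral t with n per arm in the stratum, degrees of freedom 2n − 2, and noncentrality (difference/SD) × √(n/2).
- One of five equal sites: n = 103/5 = 20.6 per arm. Power is 29.6% for SBP and 14.8% for FRS.
- Gender, SBP: 62.7% in each at 50/50; 77.4% in women and 42.0% in men at 70/30; 82.6% and 29.6% at 80/20.
- Gender, FRS: 30.6% in each at 50/50; 40.6% and 20.1% at 70/30; 45.4% and 14.8% at 80/20.

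**Step 3. Chance of a mixed pattern when the effect is the same everywhere.**

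Five sites, some significant and some not: 1 − p⁵ − (1 − p)⁵.
- SBP: 1 − 0.0023 − 0.1729 = 0.825.
- FRS: 1 − 0.0001 − 0.4497 = 0.550.

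Gender, one significant and the other not: p₁(1 − p₂) + p₂(1 − p₁).

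| Share of women | SBP | FRS |
|---|---|---|
| 50% | 0.468 | 0.425 |
| 70% | 0.544 | 0.444 |
| 80% | 0.633 | 0.467 |

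For example, SBP at 80% women: 0.826 × 0.704 + 0.296 × 0.174 = 0.582 + 0.051 = 0.633.

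**Step 4. The direct test.** In 20,000 simulated trials per setting with a common effect, an arm-by-stratum interaction F-test at 0.05 rejected in 4.8% to 5.2% of trials, for gender and for site. The same simulations gave the mixed patterns of Step 3 to within about one percentage point.

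**Step 5. Sensitivity.**
- Unequal sites (10, 15, 20, 25 and 33 per arm): mixed pattern 83% for SBP and 55% for FRS, so equal site size is not critical.
- All 250 analysed, as baseline carried forward would imply, ignoring dilution of the effect: SBP gender 41%, 51% and 62% at the three splits; SBP sites 88%.
- SBP difference of 18.3 − 7.6 = 10.7 mmHg, from the pilot means in the Background: gender 18% at 50/50 rising to 47% at 80/20; sites 94%.
- No effect at all: gender about 10%, sites about 23%.

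**Step 6. What the interaction test can and cannot do.** With 82 women and 21 men per arm (80/20), the standard error of the difference between the two SBP effects is 16.5 × √(2/82 + 2/21) = 5.7 mmHg. A true gender difference as large as 7.5 mmHg would be detected about 26% of the time (normal approximation). The test guards against false contrasts but has little power to find real ones.

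**The case against.** The strongest reply is that the sentence only promises to explore. It does not say that stratum p-values will be compared or that any subgroup conclusion will follow. Stratum estimates with confidence intervals would satisfy it and carry none of the error computed above. The model terms behind an exploratory analysis may also be in a full protocol or analysis plan that is not shown. This stands as a limit on the claim: the percentages apply only if strata are read by significance.

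A reader might infer that the trial will judge effect differences from stratum tests, and so is likely to report that the programme works in women but not in men. The documents do not support that. No such decision rule is stated, and the article aims for gender balance. At a balanced split the SBP discordance is 47%; it passes one half only from about 65% women, and for FRS it stays below one half up to 80% women. Only the site figures exceed one half on both outcomes. Nor does anything in the article tie access to the programme to subgroup results.

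It is also fair that an interaction test would have low power, so it cannot settle the question.

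What remains is that the article does name a method for site and gender, and that this method does not compare the strata. The ANCOVA and linear models it already plans could do so. The suggestion is therefore a better choice of method, not a complaint about missing detail.

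**Conclusion.** The point holds as a minor, cost-free improvement. Stratified analysis as described estimates effects within site and gender but does not test whether they differ. If strata are read at 0.05, a common SBP effect of 7.5 mmHg (SD 16.5) in 206 completers gives a mixed picture across five sites about 82% of the time (about 55% for FRS), and between men and women 47% to 63% of the time for SBP and 42% to 47% for FRS, against about 5% for an interaction test.

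The site figures rest on the article's number of sites and sample size and on equal site size, which matters little. The gender figures rest on an assumed 50% to 80% women and would be lower if the true SBP difference were 10.7 mmHg. The analysis is exploratory, and the primary comparison and its SBP power are not affected.

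**What to change.** In the Statistical analysis section, replace the sentence on stratified analysis with wording to this effect: heterogeneity of the intervention effect by site and by gender will be explored by adding arm-by-site and arm-by-gender interaction terms, one factor at a time, to the ANCOVA or linear model for change in SBP and FRS. Stratum-specific effects from those models will be shown with 95% confidence intervals, without stratum-wise significance claims. Label these analyses as exploratory, and state that the interaction tests have low power, so that a non-significant result does not show that effects are equal.

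The cost is a change of wording. It needs no extra data, visits or participants and leaves the primary analysis as it is. If an unseen analysis plan already contains these terms, the article's sentence need only be aligned with it.

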To estimate whether the intervention effect is mediated by covariates, structural equation modeling will be performed by using Mplus [74], based on the following test for mediation: Intervention ➔ Mediator (path a), Mediator ➔ Outcome (path b). Intervention status (intervention vs. wait-list control) is a binary variable specified as exogenous (i.e., not predicted by other variables in the model). Covariates, including the Time 1 value of the mediator and potential confounders, can be specified along with intervention status, as appropriate. A postulated mediator is specified as predicted by the intervention effect (path a) and the BP outcome is predicted by paths from the mediator (path b) and a direct path from the intervention (path c). This yields coefficients for the 2 paths above and their standard errors, as well as an estimate of the direct effect (path c: intervention ➔ outcome).

The hypothesized mediation pattern is a significant path from the intervention to a given mediator (e.g., self-control), and a significant path from the mediator to a given outcome (e.g., SBP), indicating that at least part of the intervention effect is due to change in the mediator. The indirect effect is analyzed as the product of the two paths divided by an estimate of its standard error [75, 76]. Mediation can be tested for individual paths or a set of paths. Fritz and MacKinnon [77] have shown that the most powerful method to apply is the bias-corrected bootstrap test, available in Mplus. Simulations show that, with modest effect sizes (standardized coefficients of .20–.25) for path a and path b above, sample sizes in the range of 120–160 participants provide .80 power to detect an indirect effect that truly exists.

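### The mediation test that the plan recommends for its power, the bias-corrected bootstrap, has a false-positive rate of about 7–8% at this trial's size when one path is zero and the other is .20–.25

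*Protocol article*

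**What the plan says.** The mediation paragraphs of the protocol article (Methods, Statistical analysis) describe the test of an indirect effect in three ways.

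- A ratio test: "The indirect effect is analyzed as the product of the two paths divided by an estimate of its standard error".
- A pattern in which both paths are significant, the second of them leading on to SBP or another outcome: "The hypothesized mediation pattern is a significant path from the intervention to a given mediator (e.g., self-control), and a significant path from the mediator".
- A bootstrap, introduced by reference to a cited simulation study: "the most powerful method to apply is the bias-corrected bootstrap test, available in Mplus".

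Power is the only reason given for the third. The supporting figure is also a power figure, and it assumes that both standardized paths lie between .20 and .25. The article puts it this way: "sample sizes in the range of 120–160 participants provide .80 power to detect an indirect effect that truly exists".

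The significance level closes the preceding text on Aims 1 and 2: "A two-tailed *p*-value <0.05 will be regarded as statistically significant". No other level is given for mediation. The expected number of completers is under Power analysis and sample size: "Assuming that 206 participants (103 per arm) complete all follow-up assessments".

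**The concern.** A test should be preferred for its power only among tests that hold the same error rate. An indirect effect is a product of two paths, and it is null whenever either path is zero. Suppose hula moves a mediator that does not drive blood pressure, or a mediator predicts blood pressure but is not moved by hula. The estimated product then has a skewed distribution whose median lies nearer zero than the estimate. The bias correction responds by moving both confidence limits away from zero, so the interval excludes zero too often. Part of the test's apparent power is this extra error.

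Aim 3 carries a stated prediction of partial mediation. The Discussion says that, if the intervention works, the mediator analysis will explain how. A statement about mechanism would then rest on a test that may run above its nominal level. The problem arises for one pre-named mediator and is separate from how many mediators are tested. A multiplicity correction presumes that each single test holds its level, so it would not cure this.

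**Working it through.** **Inputs.** From the article: 103 per arm (206 completers), 1:1 allocation, standardized paths of .20–.25, two-tailed 0.05, and the model intervention → mediator (a), mediator → outcome (b), direct path (c). Assumed, because the article does not give them: one observed mediator, normal errors, no covariates, and c = 0 unless stated.

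**Model.** M = aX + e₁ and Y = cX + bM + e₂. The indirect effect is a·b.

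**Decision rules, all applied to the same simulated trials.**
- Bias-corrected bootstrap: z₀ = Φ⁻¹(share of bootstrap products below the estimate). The limits are the bootstrap quantiles at Φ(2z₀ ± 1.96). Reject if zero lies outside.
- Percentile bootstrap: limits at the 2.5% and 97.5% quantiles.
- Joint significance: the tests of a and of b both have p < 0.05.
- Product over SE: |ab| / √(a²·SE_b² + b²·SE_a²) > 1.96. The article does not specify the SE; this is the usual first-order form.

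**Step 1: the plan's own power figure.** Power of the bias-corrected bootstrap (6,000 data sets, 1,000 resamples):

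| a = b | n = 120 | n = 160 | n = 206 |
|---|---|---|---|
| .20 | 44% | 60% | 74% |
| .25 | 71% | 84% | 93% |

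The stated 80% is reached at .25 with n between 120 and 160. It is not reached at .20 in that range. The set-up therefore reproduces the figure at the upper end of the assumed path sizes.

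**Step 2: false positives at n = 206.** 20,000 data sets, 2,000 resamples; Monte Carlo standard error about √(.07 × .93 / 20,000) = 0.18 points.

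| a | b | Bias-corrected | Percentile | Joint | Product/SE |
|---|---|---|---|---|---|
| .20 | 0 | 7.5% | 4.4% | 4.6% | 1.3% |
| 0 | .20 | 7.0% | 4.0% | 4.3% | 1.3% |
| .25 | 0 | 8.1% | 5.3% | 4.9% | 2.0% |
| 0 | .25 | 7.8% | 4.9% | 4.9% | 2.0% |

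Relative to 5%, the bias-corrected rate is 7.0/5 = 1.4 to 8.1/5 = 1.6 times nominal. The smallest excess, 2.0 points, is about 11 standard errors. Separately coded repeats gave 6.5–8.1% for the same settings.

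**Step 3: how far the excess extends.** Bias-corrected rate at n = 206, one path zero:

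| Size of the other path | Rate |
|---|---|
| 0 | 0.6% |
| .10 | 2.6–2.9% |
| .14 | 4.6–5.2% |
| .20–.25 | 7.0–8.1% |
| .30 | 7.4% |
| .39 | 6.4–6.8% |
| .59 | 5.9–6.2% |

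The .10 and .59 rows use 6,000 data sets. With a direct effect of c = .22 and the other path at .25, the rate is 7.7–8.2%. With all 250 enrolled it is 7.6% (b = .25) and 7.1% (a = .20).

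**Step 4: cost in power at n = 206.** At .20/.20: bias-corrected 74%, percentile 65%, joint 66%. At .25/.25: 93%, 90%, 90%. A separate run gave 76% against 67% and 93% against 91%.

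**The case against.** The strongest reply is that the article does not clearly commit to the bias-corrected bootstrap. The ratio sentence is the one written as a statement of what will be done. The pattern sentence asks for both paths to be significant. The bootstrap sentence reports what a cited study found and notes that software offers the method. If both paths must be significant as well, the error cannot exceed the joint-significance rate, whichever bootstrap is added. This stands in part: a reader might infer that the plan fixes the bias-corrected interval as its only test, and the text does not support that. But the pattern is given as a hypothesis rather than as a decision rule, and the bootstrap is the only method of the three that the text recommends over others. The three rules reject at about 1–2%, 4–5% and 7–8% on the same null data, so the choice between them matters.

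A reader might also infer that any mediator without an effect has a 7–8% chance of being declared one. That is wrong. The null is composite, and the rate is well below 5% when both paths are zero or the non-zero path is small. The article gives no expected paths for individual mediators, so nothing shows how often the middle band applies. Against this, a test's level is its worst case over the null, and the excess falls at the path sizes that the plan assumes.

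Three further limits stand. The 0.05 level reaches Aim 3 by reasonable inference only. The simulated model is simpler than the planned one, which allows covariates, baseline mediator values and sets of paths. The percentile bootstrap is not exactly at or below 5% either: it reached 5.3% in the main settings and slightly more when the other path was .39 or larger.

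The type of interval is often left to an analysis plan. Here, however, the article states a preference and its reason, and the reason is incomplete.

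**Conclusion.** The point holds in conditional form. At n = 206, with one path zero and the other at .20–.25, the recommended test has a false-positive rate of about 7–8% against a nominal 5%. The percentile bootstrap and joint significance stay at or near 5%, and product over SE is conservative. This rests on simulation with one observed mediator, normal errors and no covariates, and on reading the article's single significance level as covering Aim 3.

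The consequence is confined to statements about mechanism. A reader might be tempted to carry it over to the efficacy results, but the comparisons of SBP and FRS between arms use other tests and are not touched. The change is worth making because it is cheap, and because it also settles which of the three described tests decides.

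**What to change.** State one deciding test for each indirect effect: either the 95% percentile bootstrap interval, or joint significance of paths a and b at two-sided 0.05, which the article already describes in substance. State that the 0.05 level applies to Aim 3. Report the bias-corrected interval, if at all, as supportive, and drop greater power as the reason for choosing it.

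The cost is a sentence or two and one software option. At 206 completers, nominal power falls by about 7–9 points at .20/.20 (from roughly 75% to 66%) and by about 2–4 points at .25/.25 (from 93% to 90–91%). Part of that loss is the excess error being removed. The power statement for Aim 3 should be recomputed for the test chosen.

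### The stated .80 mediation power for 120–160 participants holds only near the top of the stated effect range, and the protocol does not say which test it refers to

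*Protocol article*

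**What the plan says.** The mediation paragraphs of the protocol article (Methods, Statistical analysis) set out a single-mediator model. "Intervention status (intervention vs. wait-list control) is a binary variable specified as exogenous"; path a runs from intervention to mediator, path b from mediator to outcome, and there is also "a direct path from the intervention (path c"). Covariates, among them the baseline value of the mediator, may be added.

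Three decision rules appear in succession:
- a joint pattern: "The hypothesized mediation pattern is a significant path from the intervention to a given mediator", together with a significant path from mediator to outcome;
- a ratio: "The indirect effect is analyzed as the product of the two paths divided by an estimate of its standard error";
- a resampling test: "the most powerful method to apply is the bias-corrected bootstrap test, available in Mplus".

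The power statement comes last. It claims that "sample sizes in the range of 120–160 participants provide .80 power to detect an indirect effect that truly exists". The condition attached to this claim is given as "with modest effect sizes (standardized coefficients of .20–.25) for path a and path b above". It does not say which coefficient goes with which sample size, which test is meant, or whether covariates are included.

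The general analysis paragraph sets the level: "A two-tailed *p*-value <0.05 will be regarded as statistically significant". The section Power analysis and sample size expects 206 completers, 103 per arm.

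**The concern.** The power sentence gives one value, .80, for a range of effects and a range of sample sizes. A simple calculation already makes this doubtful at the lower end. An indirect effect needs both paths, and a standardized path of .20 on its own has power below .80 with 160 people.

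Mediation is the third stated aim, and the Discussion relies on it to explain how the program lowers blood pressure. Readers will use the stated power to judge how much a null mediator result means. If .80 does not apply, such a result would be over-read as evidence that the pathway is absent. The choice among the named tests also matters, because their power differs by about 24 to 34 percentage points at the sample sizes quoted.

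**Working it through.** **Inputs from the protocol.** Paths a and b of .20 to .25, total n of 120 to 160, binary exposure allocated 1:1, two-sided 5%, and 206 expected completers.

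**Assumptions, since the protocol gives no value.** Direct effect 0 (0.20 also tried); no covariates in the base case; two-tailed 5% taken to apply to mediation.

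**Step 1: closed-form check.** Write r for the common path size and Φ for the standard normal distribution function. With no direct effect, the expected test statistics are about z_a = r√n / √(1 − r²) for path a and z_b = r√n for path b, which is adjusted for intervention. Power for both paths to be significant is about Φ(z_a − 1.96) × Φ(z_b − 1.96).

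| r | n | z_a | z_b | Power a × power b | Joint |
|---|---|---|---|---|---|
| .20 | 120 | 2.236 | 2.191 | 0.609 × 0.591 | 0.36 |
| .20 | 160 | 2.582 | 2.530 | 0.733 × 0.716 | 0.52 |
| .25 | 120 | 2.828 | 2.739 | 0.807 × 0.782 | 0.63 |
| .25 | 160 | 3.266 | 3.162 | 0.904 × 0.885 | 0.80 |

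Under the joint rule, .80 appears only in the last row.

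**Step 2: simulation of the two tests of the indirect effect.** The single-mediator model was simulated with least-squares paths. Bootstrap results rest on about 1,000 to 2,500 trials with 400 to 1,000 resamples (Monte Carlo standard error about 0.01). Separate runs agree within about 0.03 to 0.04.

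| Both paths | n | Bias-corrected bootstrap | Product over SE |
|---|---|---|---|
| .20 | 120 | 0.44 | 0.15 |
| .20 | 160 | 0.62 | 0.28 |
| .20 | 206 | about 0.75 | 0.45 |
| .25 | 120 | about 0.70 | 0.39 |
| .25 | 160 | 0.86 | 0.62 |
| .25 | 206 | 0.93 | 0.81 |

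The percentile bootstrap at 206 gives about 0.66 (runs from 0.64 to 0.68) at .20 and 0.90 at .25.

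**Step 3: where .80 is reached without covariates.** With both paths .25, the bias-corrected bootstrap gives 0.79 at n = 140 and 0.81 at n = 145. With both paths .20, it gives 0.79 at n = 220 and 0.82 at n = 230.

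**Step 4: can another reading recover the stated figure?**
- Larger effect with smaller sample: .25 at n = 120 gives about 0.70, and .20 at n = 160 gives 0.62.
- One path .20 and the other .25: 0.55 at n = 120 and 0.72 at n = 160.
- Direct effect of 0.20, both paths .20: 0.46 and 0.64.
- One-sided 5%, both paths .20: 0.60 and 0.73.
- Covariates explaining half the residual variance of mediator and outcome, both paths .20, joint rule: 0.50 and 0.67.

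None of these reaches .80 at .20/.20 with 160 or fewer.

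**The case against.** Four objections deserve weight.

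**Covariates.** The protocol allows them, and they raise power. With the bias-corrected bootstrap at n = 160, paths of .20 and .25 reach 0.80 if covariates explain 25% of residual variance and 0.90 if they explain 50%; both paths at .225 reach 0.79 and 0.82. So the limit of about .25 and 145 people applies only to the unadjusted model. These variants let the same covariates explain mediator and outcome, which mainly sharpens path a. Strong covariates acting separately in each equation would do more. At .20, n = 160 and R² = 0.50 in each, z_a = 2.582/√0.5 = 3.65 and z_b = 2.530/√0.5 = 3.58, so joint power is Φ(1.69) × Φ(1.62) = 0.90. With R² = 0.25 in each, the same formula gives 0.70. This stands as a limit on the point, but the protocol states no covariate strength and does not offer adjustment as the basis of its figure.

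**Which test is meant.** The natural reading is that the bias-corrected bootstrap is the intended inference, since it is praised just before the power sentence. That is fair, and it is why the main comparison uses that test. Even so, the figure fails over most of its range, and the ratio is described as the way the indirect effect is analysed.

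**Practical weight.** The trial is sized on systolic pressure and Framingham score and expects 206 completers. A reader might infer that real mediators would often be missed. The documents do not support this if the bias-corrected bootstrap is used: power at 206 is about 0.75 at .20 and 0.93 at .25 without covariates, and about 0.82 to 0.84 at .20 with covariates explaining 25% to 50%.

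**Type I error.** A reader might also infer that the bias-corrected bootstrap must be replaced. In one configuration (a = 0, b = .25, n = 206) it rejected about 7% to 8% of the time, against about 4% to 5% for the percentile bootstrap. That is a mild trade of error for power in one setting, and it does not rule the method out.

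**Conclusion.** The power statement is too broad. Without covariates, two-sided at 5% and with the more powerful of the two tests of the indirect effect, power runs from about 0.44 to 0.62 at .20 and from about 0.70 to 0.86 at .25 over 120 to 160 people. The stated .80 belongs only to the upper corner of that range. The text also leaves open which test the .80 describes, and product over SE falls below .80 throughout the range.

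This rests on the single-mediator model with equal paths and no covariates. Adjustment narrows the shortfall by an amount that the protocol gives no basis for fixing. It cannot be concluded that the protocol misreports its cited simulation study, because that source is not available here and may have used other conditions. Nor is the trial's size called into question. The fault lies in the stated power for the third aim.

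**What to change.** In the mediation paragraphs, or in the analysis plan:

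1. Name one deciding test for the indirect effect. Either the bias-corrected bootstrap, with a note that its type I error can run mildly above 5%, or the percentile bootstrap is acceptable. Drop product over SE as the deciding test.
2. Replace the 120–160 statement with power at the expected 206 completers, separately for .20 and .25, and state the covariate assumption. Without covariates: about 0.75 and 0.93 for the bias-corrected bootstrap, or about 0.66 and 0.90 for the percentile bootstrap.
3. If adjustment is to be credited, state the assumed share of variance explained for mediator and for outcome.

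The cost is a change of wording and a slightly less favourable stated power for the third aim. Enrolment and data collection do not change.
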